### Procedure and randomization

Prior to the start of the study, a feasibility stage has been completed, in order to check the following aspects: (1) iatrogenic effects: no harmful effects occurred; (2) feasibility check of DUDE and assessment measures: the adolescents enjoyed participating in DUDE; some of the instruments were adjusted as some pupils had difficulties understanding the questions; (3) Integrity of the emergency procedure: was not employed, but a simulation of an emergency took place. Furthermore, the communication and exchange with the two participating schools were excellent, and all parties were satisfied with the procedure. During this stage, two clinical psychologists provided DUDE, as the main aim was to check whether DUDE is accepted by the young adolescents. After this, DUDE was partially adapted with respect to some procedures or the length of certain exercises.

After the feasibility stage, the main study will start. First of all, the schools for the main study will be chosen by the Ministry of Education and Cultural Affairs. The respective school principals will then be contacted to ensure that the implementation of the study will run smoothly. This will be followed by a personal meeting with the teaching staff and the study team to inform about the rationale, aims, and study procedure. At this point, schools will not yet have been randomly assigned to a trial group. This should prevent any bias due to motivational effects during the recruitment. Once schools have given consent, pupils and parents will receive information about the study in the following order: (1) An information evening (1 ½ h) about the study will be held for parents and pupils. (2) Subsequently, parents and participants will once again receive all information in writing and the consent form via mail or e-mail. (3) To give the participants another opportunity to ask questions, information about the study will be provided again (during a regular lesson) before data collection, and the presence of the consent forms will be checked. The written and oral information will include the following: background and objectives of the study, information about the prevention program (DUDE) and minimal intervention, benefits and possible risks of participation, data collection procedures, and data security procedures. After parents and adolescents have received the required information, informed consent will be obtained. The parents and participants will confirm with their signature that they have read and understood the provided information and that they are willing to participate. Nevertheless, they will be able to withdraw from the study at any time without any consequences for subsequent school matters or medical care (see also the “Ethical issues and dissemination” section). Next, schools will be randomized. Before the baseline measurement, pupils will be checked for eligibility and the booklets (“Stress-free through the school day”) will be handed out. Seven days (± 3 days) after the baseline measurement, DUDE will conducted in treatment groups 1 and 2 and will be integrated into the normal school schedule.

Given the very large number of over 3000 participants, the measurements and execution of DUDE will be split into two time points. We aim to begin in November 2021, and the second round of assessment should take place around March 2022. However, due to the SARS-Covid-19 pandemic, delays are possible. To ensure that enough individual pupils give their consent to participate, the DUDE training will be integrated into the regular school day, during lesson time, to make participation more attractive to the students.

As mentioned above, to prevent bias, 16 schools will be randomly (cluster randomization, see the “Discussion” section) assigned to DUDE or to the active control group, with eight schools per group, using cluster randomization. Within the treatment group, there will be a secondary randomization into treatment groups 1 or 2. Enrolment, generation of allocation sequence, and assignment of schools will be carried out using the software SAS by an independent member of the institute not involved in the project. The schools will be informed about their group affiliation via e-mail and telephone call immediately after randomization. Nevertheless, blinding is not completely possible, as schools cannot be blinded to the different nature of the interventions. Blinding of the researchers is also not possible because the treatment group will receive DUDE in addition to the minimal intervention.

### Data assessment

Data will be collected and assessed in cooperation with the Institute of Clinical Epidemiology and Biometry, University of Wuerzburg, Germany. The baseline assessment (T0) will take place after randomization and 7 days (± 3 days) before the subsequent start of the treatments. At the end of DUDE or 5 weeks after receiving the minimal intervention (± 7 days), the second measurement (T1) will be conducted. Further assessments will ensue 6 months (± 7 days; T2) and 12 months (± 7 days; T3) after the end of DUDE. After every measurement, the data will be screened for potential suicidality (see the “Emergency procedure” section). At T2, only a selection of the assessment measures will be used (see Fig. 2). We chose this procedure in order to check for iatrogenic effects which could occur immediately after the prevention [24], whereas protective effects, or rather efficacy, in universal prevention is expected later [25]. Additionally, we will evaluate how appealing DUDE is to the adolescents, as this might have an impact on the effectiveness of the program.

### Assessment measures

T0 includes sociodemographic questions gathering information about gender, nationality, status of mental health treatment, current living situation, media consumption, and the socioeconomic status of the families, as measured with the brief version of the Family Affluence Scale (FAS III). The FAS III is a revised version of the Family Affluence Scale [26–28] which was validated in 7120 pupils from several European countries and appears to be a valid instrument to measure socioeconomic status [29]. In accordance with Good Clinical Practice (GCP), primary and secondary outcomes will be assessed.

#### Primary outcome

For the assessment of NSSI, we will use a modified version of the 9-item *Deliberate Self-Harm Inventory* (DSHI-9), which was used in the SEYLE study [12]. The original version of the DSHI, by Gratz, contains 17 items [30], and the DSHI-9 is an adaptation for adolescents by Lundh [31]. The modified version comprises the same facets on frequency, severity, and duration of NSSI as the 9-item version; however, self-injurious acts are combined in order to simplify and shorten the measure and to assess direct self-injury to one’s body surface only [32]. The internal consistency for the DSHI-9 lies between alpha = .66 and .85 [33].

#### Secondary outcomes

Emotion regulation will be assessed using the DERS-SF [34], an 18-item short version of the original 36-item *Difficulties in Emotion Regulation Scale* [35, 36]. The DERS-SF measures emotion regulation on six dimensions (Lack of Emotional Awareness, Nonacceptance of Emotional Responses, Difficulties Engaging in Goal-Directed Behavior, Limited Access to Emotion Regulation Strategies, Impulse Control Difficulties, Lack of Emotion Clarity). Cronbach’s alphas are .79–.91 for the subscales and 0.98 for the total score [37]. Thus, the DERS-SF is capable of measuring emotion regulation deficits to the same extent as the original DERS [34, 37].

The *Paykel Suicide Scale* (PSS) [38] is a short questionnaire consisting of five items exploring suicidal ideation and previous suicide attempts. A modified version with the following three response options will be used: “within the last two weeks,” “at some point in the past,” or “never”. Psychometric properties are difficult to find in the literature; however, the PSS has been used for many years to assess suicidality in adults and adolescents [39–43].

The *KIDSCREEN-27* will be used to assess participants’ general health-related quality of life (HRQoL). The scale was developed across Europe for use in children and adolescents (aged 8–18 years) [44, 45] and consists of 27 items measuring HRQoL on 5 scales (Physical Well-being, Psychological Well-being, Parents & Autonomy, Social Support & Peers, School Environment). It is a commonly used valid instrument with high internal consistency (Cronbach’s α range from .78 to .84) [44, 45].

The revised *Regulatory Emotional Self-Efficacy Scale* was developed to assess self-efficacy beliefs in the domain of emotion regulation (RESE-R) [46, 47]. It contains 12 items rated on a Likert scale from 1 (= not at all well) to 5 (=very well) and is composed of two subdimensions: One represents the perceived self-efficacy in expressing positive emotions (POS) and the other represents the perceived self-efficacy in expressing negative emotions (NEG). The negative dimension constitutes a second-order factor with two factors: self-efficacy in managing despondency/ distress (DES) and self-efficacy in managing anger/ irritation (ANG). Good internal consistencies for the individual areas have been reported (*α* = .68 to .79) [46].

To assess emotional and behavioral difficulties, or rather general psychopathology, the *Strengths and Difficulties Questionnaire* (SDQ) [48] with 25 items will be used. The SDQ collects information about problems and resources in the areas of emotional problems, hyperactivity/ attentional problems, problems with peers, behavioral problems, and prosocial behavior. A study evaluating the reliability and validity of the German version of the SDQ indicated that the questionnaire is valid for most clinical and research purposes [49]. Moreover, the SDQ shows good internal consistency (*α* = .81) [50].

For the assessment of depressive symptoms, the 9-item *Patient Health Questionnaire* (PHQ-9) will be used. The PHQ-9 measures depressive symptoms according to the DSM-IV criteria in a self-administered assessment, which has been found to have high sensitivity (89.5%) and good specificity (78.8%) [51]. The scale meets the clinical diagnostic criteria according to the ICD-10 (International Classification of Diseases, 10^th^ Revision) and has shown high sensitivity (87.1%) and good specificity (79.7%) among adolescents, with a good rtt = .87 and good internal consistency (Cronbach’s *α* = .83) [52].

The Short Evaluation of Eating Disorders questionnaire (SEED) [53] consists of six items and allows the calculation of severity indices of anorexia nervosa (underweight, fear of weight gain, distortion of body perception) and bulimia nervosa (binge eating, compensatory behavior, excessive overconcern with weight, and body shape). The questionnaire has good construct and criterion validity. The sensitivity to change also ensures that treatment changes can be assessed. The questionnaire has been used successfully in prevention studies in this age group [54]. We will measure eating disorder psychopathology because starving, vomiting, and binge eating are sometimes used as dysfunctional behavior in adolescents with problems in emotion regulation [55] and are strongly associated with NSSI [56].

#### Process and adherence variables

We assess process variables among pupils to determine whether and how much students liked DUDE. If pupils indicate that they liked the program, we assume increased motivation during participation, which could be associated with better transfer to everyday life. In addition, we survey the adherence of the trainers. It is important to check whether the manual is followed and how the success of DUDE is evaluated after each implementation. We assume that the adherence and the attitude of the trainers towards the program could also have an impact on the efficacy of the program.

In line with this rationale, additional items will be presented to evaluate both the DUDE program itself and the booklet (“Stress-free through the school day”). On a 6-point Likert scale, participants will rate six items regarding how helpful they found the different chapters of the booklet to be, and 10 items regarding how helpful they found the sessions of the training to be, whether they liked the implementation of the program and what they learned during the training.

Program adherence of the clinical psychologist or teachers will also be measured using a self-constructed instrument. Five items ask about how satisfied the teachers are with the sessions, whether they think the program was helpful, and about the cooperation of the students. Furthermore, to verify whether the coaches stuck to the manual, a checklist will be used to determine whether they implemented the specific contents of every lesson.

#### Confounding variables

The confounding variables control for whether students are open to the changes DUDE might bring about in their thoughts, feelings, and/or behavior (willingness to change) and how exposed they were/are to the SARS-Covid-19 pandemic-related consequences, as both factors could influence primary and secondary outcomes.

Willingness to change is increasingly cited as an important variable in health behaviors, and a predictor of treatment success: The *University of Rhode Island Change Assessment* (URICA) scale is used to measure patients’ motivation to learn and change [57]. Willingness to change is assessed according to four subscales (Precontemplation, Contemplation, Action and Maintenance) and the psychometric properties have been found to be good, with coefficient alphas from .79 to .89 [58]. In this study, a briefer and modified version of the German translation, called *Fragebogen zur Erfassung der Veränderungsbereitschaft* (FEVER [59];), will be used. This comprises 24 items which have been semantically adapted to match the prevention program and will assess the pupils’ willingness to change by asking about whether they are keen to participate, willing to try the strategies they are taught in the program, and their impression of the trainers [59].

Finally, ten questions regarding the SARS-Covid-19 pandemic will be asked, which explore stress factors, general mood, and well-being in families during the pandemic. These questions are from the Corona Health App, which was developed as part of a scientific cooperation between university partners, the Robert Koch Institute, and software companies (for detailed information see, https://www.corona-health.net).

### Interventions

*N* = 3200 participants in 16 schools (8 per group) will be cluster-randomized to the treatment groups, providing the minimal intervention as well as DUDE, and the active control group, providing only the minimal intervention. Table 1 provides an overview of the minimal intervention and Table 2 an overview of DUDE.

**Table 1 Tab1:** Overview of booklet “Stress-free through the school day” goals, content, and targeting risk factors

Booklet unit	Goals	Content	Targeted risk factors
1. General information	• To increase knowledge and sensitivity regarding stress	• Definition of stress • Description of positive and negative consequences of stress • List of overload signs	• Improving the ability to identify stress and overloads (especially at school)
	• To deal with stress at school	• Different causes of school stress • Test: How stressed are you?	
2. How to prevent stress	• To gain techniques for efficient learning	• Tips to get started • Tips to avoid distraction • Tips for a better time management • Presentation of specific cognitive learning strategies	• Improving stress management • Strengthen body and mind • Internalizing suitable learning strategies
	• To strengthen resources and vitality	• Nutrition tips • Tips to establish healthy sleep habits • Tips to relax • Meaning of positive thoughts	
3. Getting help	• To seek help if necessary	• Overview and importance of the social network • Overview of unhealthy ways to deal with stress	• Lower inhibition threshold to seek help
	• To have contact addresses within reach	• Summary of possible points of contact

**Table 2 Tab2:** Overview of DUDE goals, content, and targeting risk factors

DUDE unit	Goals	Content	Targeted risk/protective factors
1 – Feelings are like Waves	• To introduce to the topic / to commit to the program	• Introduction Video • Introduction and information regarding DUDE	
	• To build solidarity in the class	• Activating “Get to know Game” • Joint development of class rules	• Encouraging social support within the class
	• To improve one’s emotional perception and awareness	• Interactive group game regarding emotions • Exercise for the mindful perception of emotions	• Improving the ability to identify, differentiate and express one’s own feelings
2 – Overwhelmed by Feelings	• To improve awareness about stress and emotional tension	• Activating group game to show that everyone experiences stress • Guided group discussion to introduce the concept of “aversive emotional tension	• Improving stress management
	• To gain adaptive skills to deal with daily struggles	• Collection of stress tolerance skills in small groups • Class discussion of pros and cons of specific skills • Group game in which students train skills to prevent impulsive reactions	• Training impulse control
3 – Riding the Wave of Feelings	• To recognize the importance of emotion regulation	• Video about emotionally stressful events being handled maladaptive • Joint acquisition of the different stages of emotion regulation by referring back to the video	• Increasing the access and flexibility to different emotion regulation strategies
	• To improve one’s ability to regulate – especially negative - emotions	• Interactive exercises and role plays to train various mood-stabilizing skills	• Reducing negative affect
4 – What gives you boost?	• To learn to rely on oneself	• Group brainstorming about resources • Mindfulness-based exercise to train radical acceptance • Introspective exercise to become aware of own strengths and abilities	• Improving self-esteem and self-efficacy
	• To improve one’s interpersonal skills	• Group game in which the students must collaborate • Group exercise to train benevolent and respectful interaction with one another	• Counteracting bullying by an improved class climate and enhanced interpersonal abilities
5 – Jump into the wave’	• To anchor knowledge in everyday life	• Repetition of program contents and acquired strategies • Definition of intentions: “What do I want to implement in everyday life?”	• Improving self-efficacy by encouraging self-responsibility

#### Minimal intervention

Within the minimal intervention, information material (a booklet called “Stress-free through the school day”) on the subject of how to handle stress, especially at school, will be distributed. This form of universal prevention follows the principles of a mental health literacy prevention program. The booklet provides general information on stress, its possible negative outcomes, and ways to prevent it. Moreover, cognitive techniques are outlined which help to make learning more efficient and consequently less stressful. For detailed information on the program goals and content, see Table 1.

#### DUDE

The development of the program was preceded by a systematic review of the literature. Targeted prevention, which significantly reduces NSSI and improves mental health, is based on elements of cognitive behavioral therapy (CBT) and dialectical behavior therapy (DBT) [14, 60]. The main goal of these approaches is to find alternative behaviors for NSSI against the background of an improved emotion regulation. Deficits in emotion regulation, especially in terms of coping with uncomfortable feelings and relief from emotional stress or pressure, are the most common reasons for NSSI [61]. A recently published meta-analysis also revealed a significant association between emotion dysregulation and NSSI, with emotion dysregulation encompassing limited access to regulation strategies, non-acceptance of emotional responses, impulse control difficulties, and difficulties engaging in goal-directed behavior [62].

These factors should be addressed in an effective universal prevention and a skills-based approach seems reasonable to achieve this (see the “Background” section for further information).

DUDE includes five 90-min units conducted at weekly intervals. The didactic methods consist of skills coaching, including interactive methods (experience-based approaches, group discussion and role plays) and theme-specific cartoons (videos) to anchor the content. Homework has to be completed after every lesson in order to integrate the content into the adolescents’ daily routine. A tandem of a male and a female clinical psychologist or teacher (depending on treatment group) will conduct DUDE. In accordance with the metaphor of Kabat-Zinn [63] “You can’t stop the waves but you can learn to surf,” meaning that emotions cannot be prevented but one can learn how to deal with them, DUDE is set up as an imaginary surf camp. The five units are (1) “Feelings are like waves,” (2) “Overwhelmed by feelings,” (3) “Ride the wave of feelings,” (4) “What gives you boost?,” and (5) “Jump into the wave.” For detailed information on the program goals and content, see Table 2.

### Emergency procedure

If the participants report serious suicidal thoughts in one of the measurements (assessed with the PSS, especially item 4 “Have you ever reached the point where you seriously considered taking your life or perhaps made plans how you would go about doing it?,” answering “Yes, within the last two weeks”), there will be an immediate (within 24 h) report back to their family. The family will be informed about the situation by one of the principal investigators and an appointment with a personal contact will be made at the Department of Child and Adolescent Psychiatry, University Hospital of Wuerzburg, or in one of the admission clinics with which the study team is cooperating. During this appointment, suicidality will be examined and, if necessary, a treatment offer will be made. If adolescents indicate serious suicidal thoughts within a unit of DUDE, psychologists or teachers will telephone the psychiatrist on duty to clarify the situation in a first step, and subsequently inform one of the principal investigators, as needed. Over the entire duration of the study, participants and their caregivers will be able to contact the Department of Child and Adolescent Psychiatry, University Hospital of Wuerzburg, in the case of mental health problems. This will also be indicated in the information letter.

### Coaches

In treatment group 1, DUDE will be administered by psychologists. The psychologists have completed an undergraduate psychology degree, and at least one member of each tandem providing DUDE in schools is currently in training to become a clinical psychologist. In treatment group 2, DUDE will be implemented by trained teachers. All coaches will have taken part in a 1-day course to prepare them for conducting the program and will additionally receive an implementation manual in order to standardize the procedure. Furthermore, there will be the possibility for weekly supervision if requested from the coaches.

### Sample size

The primary endpoint is the incidence of NSSI measured by the dichotomized DSHI-9 at T3. We assume an incidence rate (newly detected cases in the last 12 months) of 2.31% in the control group and 0% in the treatment group. This assumption is based on data from a longitudinal study by Baetens et al. [64], which reported a prevalence of 3% in the control group at age 12–13 years and a prevalence of 5.31% later at age 14–15 years. We hope that due to our prevention program, no new cases will occur in the treatment group and assume a stable prevalence rate of 3%. In the active control group, an increase from 2.31 to 5.31% in 1 year can be assumed based on the data of Baetens [64].

To account for the need for cluster randomization in our study, we need to calculate an intraclass correlation coefficient (ICC). We assume an ICC of 0.015. As there was no ICC available for NSSI, this assumption is based on data from two studies of binge drinking behavior in adolescents [65, 66]. Comparability between NSSI and binge drinking can be expected, as both represent maladaptive strategies for coping with one’s own feelings or for dealing with personal stress.

We plan to recruit 160 pupils per school (four classes per grade, 6th and 7th grade (age 11–14 years)). A two-sided unpooled *z*-test for cluster-randomized studies will be used to test the null hypothesis of equal proportions. A sample size of 160 pupils per school and eight schools per group yields a power of 80% to detect a difference between the proportions of 2.31%. The significance level will be set at 5%. Including a dropout rate of 20%, 200 pupils per school and a total number of 3200 pupils need to be recruited. The sample size was estimated using PASS 15.05.

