**Methods:**

The main objective of the present study is to evaluate a newly developed universal prevention program (“DUDE – Du und deine Emotionen / You and your emotions”), based on a skills-based approach in schools, in 3200 young adolescents (age 11–14 years). The effectiveness of DUDE will be investigated in a cluster-randomized controlled trial (RCT) in schools (*N* = 16). All groups will receive a minimal intervention called “Stress-free through the school day” as a mental health literacy program to prevent burnout in school. The treatment group (*N* = 1600; 8 schools) will additionally undergo the universal prevention program DUDE and will be divided into treatment group 1 (DUDE conducted by trained clinical psychologists; *N* = 800; 4 schools) and treatment group 2 (DUDE conducted by trained teachers; *N* = 800; 4 schools). The active control group (*N* = 1600; 8 schools) will only receive the mental health literacy prevention. Besides baseline assessment (T0), measurements will occur at the end of the treatment (T1) and at 6- (T2) and 12-month (T3) follow-up evaluations. The main outcome is the occurrence of NSSI within the last 6 months assessed by a short version of the Deliberate Self-Harm Inventory (DSHI-9) at the 1-year follow-up (primary endpoint; T3). Secondary outcomes are emotion regulation, suicidality, health-related quality of life, self-esteem, and comorbid psychopathology and willingness to change.

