### Objectives and aims

The main objective of the present study is to evaluate a newly developed universal prevention program (“DUDE – Du und deine Emotionen / You and your emotions”) based on a skills-based approach in schools, in 3200 young adolescents (age 11–14 years). The effectiveness of DUDE will be tested in a cluster-randomized controlled trial (RCT), meaning that the participating schools (*N* = 16) will be randomly assigned to the respective conditions (see the “Procedure and randomization” section). All groups will receive a minimal intervention with a booklet called “Stress-free through the school day” as a mental health literacy prevention against burnout in school. The treatment group (*N* = 1600; 8 schools) will be divided into: treatment group 1 (DUDE will be conducted by trained clinical psychologists; *N* = 800; 4 schools) and treatment group 2 (DUDE will be conducted by trained teachers; *N* = 800; 4 schools). The active control group (*N* = 1,600; 8 schools) will only receive the mental health literacy prevention. The main outcome is the occurrence of NSSI within the last 6 months assessed by a short version of the Deliberate Self-Harm Inventory (DSHI-9) at the 1-year follow-up (primary endpoint; T3). We hypothesize that DUDE will show a lower incidence of NSSI compared to the active control group, demonstrating its superiority. In addition, secondary outcomes such as emotion regulation and suicidality, health-related quality of life, self-esteem as well as comorbid psychopathology, and willingness to change will demonstrate the superiority of DUDE over the active control group.

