### Primary hypothesis

Participants in the treatment group (1 or 2) receiving DUDE will show a lower occurrence of NSSI within the past 6 months at T3 compared to students in the active control group.

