### Statistical analysis

The primary hypothesis will be addressed by using a univariate generalized linear mixed-effects model with logit link function for the probability of newly detected NSSI (measured dichotomously) at T3. To model the correlation within schools, schools will be included as random effects.

As secondary analyses, the generalized linear mixed model for the primary outcome will be adjusted for potential sociodemographic confounders (sex, socioeconomic status, mental stress due to the COVID-19 pandemic). In addition, we will adjust the baseline measure NSSI, although our analysis will only consider the incidence rate (newly detected NSSI in the last 12 months). Furthermore, based on the distribution of the secondary outcomes, differences in secondary outcomes between the two groups (treatment and intervention) will be compared. We will analyze emotion regulation (DERS-SF), suicidality (PSS), quality of life (KIDSCREEN-27), self-efficacy (RESE-R), general mental health (SDQ), depression (PHQ-9), and eating disorder pathology (SEED) using univariate mixed-effects models, and with non-parametric tests if necessary due to the data material.

Missing data and individuals who withdraw from the trial will be handled using an intention-to-treat (ITT) approach. All participants randomized will be considered in the analysis. In the case of dropout or missing data, we will use the multiple imputation method.

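### The primary endpoint is worded in two ways (6-month occurrence at T3, and newly detected NSSI over 12 months), and the stated 80% power belongs only to the second

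*Protocol article*

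**What the plan says.** All references are to the protocol article.

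- **Abstract (Methods):** "The main outcome is the occurrence of NSSI within the last 6 months", assessed at the 1-year follow-up. Objectives and aims repeats this definition, then speaks of a lower incidence in the hypothesis that follows.
- **Primary hypothesis:** pupils receiving DUDE "will show a lower occurrence of NSSI within the past 6 months at T3 compared to students in the active control group". It sets no condition on NSSI status at T0.
- **Sample size:** "The primary endpoint is the incidence of NSSI measured by the dichotomized DSHI-9 at T3". The rates are new cases: "We assume an incidence rate (newly detected cases in the last 12 months) of 2.31% in the control group" and 0% in the treatment group. The bridge from prevalence to incidence is the hope that "no new cases will occur in the treatment group and assume a stable prevalence rate of 3" per cent, against 5.31% in the control group. The design "yields a power of 80% to detect a difference between the proportions of 2.31" per cent.
- **Statistical analysis:** the primary model is a mixed model with "logit link function for the probability of newly detected NSSI (measured dichotomously) at T3". Adjustment for baseline NSSI appears only among the secondary analyses, with the remark that the analysis looks only at new cases in the last 12 months. The same section says that all randomised participants enter the analysis.

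**The concern.** The two wordings differ in who can be a case and in how far back the question reaches. Under the hypothesis, a pupil who already self-injured at T0 and still does so at T3 counts. Under the sample size and model, that pupil does not. A pupil who starts after the programme and stops more than 6 months before T3 is a new case over 12 months, but is missed by a 6-month recall at T3.

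Two primary results could therefore be computed from the same data, each with support in the text. The power statement also attaches to only one of them. The plan describes its 80% as power for a difference of 2.31 percentage points, but that difference has very different power at 2.31% v 0%, where one arm contributes no variance, and at 5.31% v 3.00%. A null result for the hypothesis as worded would be read against a power that was not calculated for it.

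**Working it through.** **Inputs (Sample size section):** 8 schools per group, 160 analysed pupils per school, ICC 0.015, two-sided 5%, unpooled z-test for cluster-randomised proportions. New-case rates are 2.31% v 0%; prevalences are 5.31% (control) and 3.00% (DUDE). Both pairs differ by 2.31 points (5.31 − 3.00 = 2.31).

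**Formulae**

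- Design effect = 1 + (160 − 1) × 0.015 = 3.385.
- Effective n per arm = 8 × 160 / 3.385 = 378.1.
- SE = √{[p₁(1 − p₁) + p₂(1 − p₂)] / 378.1}.
- Power = Φ{(p₁ − p₂)/SE − 1.96}. The t variant uses a noncentral t with 2 × (8 − 1) = 14 df.

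**Step 1. The plan's own figure (2.31% v 0%)**

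SE = √(0.0231 × 0.9769 / 378.1) = 0.00773 and z = 0.0231/0.00773 = 2.99, so power is 84.9%. With t on 14 df it is 79.4%. The z-test with 0.1% in place of exactly 0% gives 79.9%. The stated 80% is thus reproduced for newly detected cases by either variant. The article does not say what value was entered for 0%.

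**Step 2. The hypothesis as worded (5.31% v 3.00%)**

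Assumption: both prevalences are 6-month rates.

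SE = √[(0.0531 × 0.9469 + 0.03 × 0.97) / 378.1] = 0.01449 and z = 0.0231/0.01449 = 1.594, so power is 35.7% by z and 31.8% by t.

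The ICC is borrowed from binge-drinking studies, so its effect should be shown:

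| ICC | Power by z, 5.31% v 3.00% |
|---|---|
| 0.005 | 59% |
| 0.01 | 45% |
| 0.015 | 36% |
| 0.02 | 30% |

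**Step 3. The bridge between the definitions**

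Unless the cited prevalences are lifetime figures, a stable 3% equals no new cases only if no baseline case stops. If a share s of the 3% stops by T3, holding 3% (DUDE) and reaching 5.31% (control) requires new cases of 3s% and (2.31 + 3s)%, as proportions of all pupils. The documents give no value for s, so the full range is shown:

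| s | New cases, control v DUDE | Power by z |
|---|---|---|
| 0% | 2.31% v 0% | 84.9% |
| 10% | 2.61% v 0.30% | 76.0% |
| 25% | 3.06% v 0.75% | 64.5% |
| 50% | 3.81% v 1.50% | 50.8% |
| 75% | 4.56% v 2.25% | 41.9% |
| 100% | 5.31% v 3.00% | 35.7% |

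**Step 4. Sensitivity of the new-case power to exactly 0%**

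With control held at 2.31%, the same formula gives 79.9% at a DUDE rate of 0.1%, 56.4% at 0.5% (0.0181/0.00853 = 2.121) and 29.3% at 1.0% (0.0131/0.00927 = 1.414).

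**Step 5. Effect of limiting the primary set**

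Removing about 3% of pupils leaves 160 × 0.97 ≈ 155 per school. At 2.31% v 0% this gives 84.5% by z and 79.0% by t, so the restriction costs almost nothing.

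**The case against.** The strongest reply is that the power calculation and the planned primary analysis agree. The Statistical analysis section says the primary hypothesis will be tested with a model for newly detected NSSI, and newly detected NSSI is what was powered. Objectives and aims also speaks of a lower incidence. On this view the defect is loose wording in the hypothesis plus an unreconciled window. This largely stands. A reader might infer that the 80% was computed for a different analysis from the one planned, and the documents do not support that.

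Second, a reader might take 36% as the trial's established power. It is not. The 3% and 5.31% come from a cited longitudinal study whose recall window the article does not give, and the result moves with the ICC. The 36% is conditional, although these are the only prevalences the article offers for the two arms.

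Third, if those prevalences are lifetime figures, a stable 3% does mean no new cases, whoever stops. That reading cannot be excluded, and no single stopping share has support in the documents.

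Fourth, one might want to count onset at T1 or T2 so as to cover the full 12 months. Every section that defines the endpoint agrees on T3, and the T2 measures are listed in a figure not available here, so the remedy should not depend on that.

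What survives is the contradiction: the section headed Primary hypothesis and the abstract state one endpoint, the sample size and model use another, and no text joins them.

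**Conclusion.** The point holds as an internal inconsistency in the primary endpoint, in both population and look-back window. The stated 80% belongs to newly detected NSSI at 2.31% v 0%, and to that definition only. For the hypothesis as worded, power is about 36% by z (32% by t), provided the cited prevalences are 6-month rates and the ICC is 0.015. Over ICCs of 0.005 to 0.02 it is 59% to 30%, and none of these values reaches 80%. Even for new cases, the 80% requires essentially none under DUDE. If the prevalences are not lifetime figures, power by z runs from 85% down to 36% as the share of baseline cases that stop goes from none to all. The contradiction itself rests on the text alone; the size of the power loss rests on the stated assumptions.

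**What to change.** Keep T3, and use one population and one look-back window in the abstract, aims, primary hypothesis, sample size and primary model. There are two ways to do this.

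(a) **New onset.** Define the primary endpoint as newly detected NSSI at T3 among pupils without NSSI at T0. Align the abstract, aims, hypothesis and recall window with this, limit the primary analysis set to those pupils, and reconcile that set with the statement that all randomised participants are analysed. State the 80% as conditional on 0% new cases in the DUDE arm, and give the power for non-zero rates beside it.

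(b) **Occurrence.** Keep 6-month occurrence at T3 in all pupils and move T0 NSSI into the primary model as a covariate. Replace the 80% by about 36% (unadjusted, 5.31% v 3.00%, ICC 0.015), with the recall-window assumption and the ICC range stated.

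The cost is protocol and registry wording. Option (a) also takes about 3% of pupils out of the primary set; option (b) states a less favourable power, which it discloses but does not repair. Neither needs extra pupils.
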